## Abstract

Several cognitive training programs, alone or in combination with non-invasive brain stimulation have been tested in order to ameliorate age-related cognitive impairments, such as the ones found in Mild Cognitive Impairment (MCI). However, the effects of Cognitive Training (CT)—combined or not—with several forms of non-invasive brain stimulation have been modest at most. We aim to assess if Speed of Processing (SoP) training combined with alpha transcranial alternating current stimulation (α-tACS) is able to increase speed of processing as assessed by the Useful Field of View (UFOV), when comparing to SoP training or active α-tACS alone. Moreover, we want to assess if those changes in speed of processing transfer to other cognitive domains, such as memory, language and executive functioning by using the NIH EXAMINER. We also want to test the mechanisms underlying these interventions, namely brain connectivity and coherence as assessed by electroencephalography (EEG). To that purpose, our proposal is to enroll 327 elders diagnosed with MCI in a double-blinded, parallel randomized clinical trial assessing the effects of combining SoP with alpha endogenous tACS (either active or sham) in people with MCI. Participants will perform an intervention that will last for 15 sessions. For the first 3 weeks, participants will receive nine sessions of the intervention, and then will receive two sessions per week (i.e., booster) for the following 3 weeks. They will then be assessed at 1, 3, and 6 months after the intervention has ended. This will allow us to detect the immediate, and long-term effects of the interventions, as well as to probe the mechanisms underlying its effects.

**Clinical Trial Registration:**
Clinicaltrials.gov, Identifier: NCT05198726.

## Introduction

The major predictor for cognitive decline is age (Tilvis et al., 2004; Schaeverbeke et al., 2021). Despite heterogenous profiles in terms of progression and severity, a dysexecutive syndrome that can be detected in early onset variants of Alzheimer’s disease (Townley et al., 2020), or in mild cognitive impairment (i.e., MCI; Blanco Martín et al., 2016) has been commonly reported. This dysexecutive syndrome translates to difficulties in terms of crystalized and fluid intelligence, processing speed, attention, memory, language, and executive functioning (Harada et al., 2013), and as such, constitute potential targets for cognitive training (CT) in these populations.

In the absence of official number for the lifetime prevalence of MCI, a recent meta-analysis suggested that MCI can affect from 22.5 (aged 75–79) to 60.1 persons (aged 85 years or older) per 1,000 persons-year (Gillis et al., 2019). Moreover, several studies suggested that people with MCI are more prone to develop dementia (Baker et al., 2008), especially if the degree of functional baseline is accounted for (Farias et al., 2009). However, there are also some reports that people with MCI reverted their cognitive condition to a normal stage (Hu et al., 2020). This is especially important because, this may end up lowering the risk of developing dementia for some people with MCI. Furthermore, even with the recent advances in terms of medication, especially the aducanumab, its impact on cognition is still a matter of intense debate (Walsh et al., 2021).

In that sense, several interventions under the general umbrella of CT have been extensively studied in order to test if CT, will be able to minimize or revert the effects of age-related cognitive decline in older adults (Irazoki et al., 2020 for review; Willis et al., 2006). For instance, a program using cognitive training in people with MCI that consisted of 60-min sessions, 3 times a week, during 6 months was able to induce a medium size effect improvement in the Alzheimer’s Disease Assessment Scale-Cognitive Subscale (ADAS-Cog; Train the Brain Consortium, 2017). Moreover, previous meta-analyses suggested that cognitive training in healthy volunteers can indeed increase fluid intelligence (Karbach and Verhaeghen, 2014; Au et al., 2015). However, other meta-analysis suggested that the effects of CT in the elderly are modest at most (Teixeira-Santos et al., 2019).

Interestingly enough, a recent randomized clinical trial (RCT) with 10 years of follow-up, compared the efficacy of three types of cognitive training in 2,802 older adults. In this trial, participants received either Working memory, Reasoning or Speed of Processing training compared to a waiting list. The CT consisted of 10 sessions during six weeks, and then up to four booster sessions at the 11th month, and finally another up to four booster sessions at the 35th month. Working memory or reasoning training did not reduce the risk of developing dementia [43% met the diagnosis of dementia criterion, 28% met the Mini Mental State Examination (MMSE) criterion, 12% met the psychometric criterion; 15% and 2% met all three criteria] when compared to controls, but that was not the case for speed of processing (SoP) training (Edwards et al., 2017). In another study, SoP training increased participant’s instrumental everyday abilities, including driving abilities (Ball et al., 2007). Moreover, transfer effects to other cognitive domains (e.g., attention, memory) and increases in connectivity within the brain’s central executive network following SoP training were also reported (Lin et al., 2016). This is not surprising, as SoP has been shown to be an important marker for individual differences in terms of structural connectivity (Bennett and Madden, 2014). Moreover, higher order cognitive functions, such as executive functioning, rely on efficient communication between brain regions, and as such, decreases in SoP are a strong predictor of age-related decline in several cognitive domains (Gao et al., 2020). This reflects a connection deterioration between distal brain regions in what has been called the “disconnected brain” framework (Fjell et al., 2013). Thus, an increase of target engagement may be possible by tuning-in the neural population towards the trained ability, by using non-invasive brain stimulation (NIBS).

We have previously shown that we were able to modulate cognition using transcranial direct current stimulation (tDCS), namely on executive functioning (Leite et al., 2011, 2013), working memory (Carvalho et al., 2015a), empathy (Rêgo et al., 2015), approach/avoidance motivation underlying craving (Carvalho et al., 2018), attention and pain (Silva et al., 2017; Santos et al., 2018). Furthermore, by understanding the underlying mechanisms of the intervention in the brain, it is possible to develop neural based interventions, whose ultimate aim is to optimize the target engagement (Carvalho et al., 2015b).

One possible way of doing so, is to combine SoP training with another technique— transcranial alternating current stimulation (tACS) —which has been shown to entrain brain activity (Antal and Herrmann, 2016). Entrainment refers to the frequency dependent response of brain waves in order to match the frequency of the stimulus that are being applied to the brain (Huang and Charyton, 2008). Alpha entrainment may be of particular interest for SoP. For instance, a study has already showed that speed of processing is associated with changes in this specific band (Hilla et al., 2020). By combining the two interventions, it will be hypothetically possible to optimize brain communication between distal regions, and thus, increase cognitive performance. According to the Communication through Coherence hypothesis (CTC), effective connectivity requires rhythmic synchronization between pre and post synaptic neurons and their coherence. Thus, in the absence of coherence, inputs arrive at random phases of the excitability cycle, which result in lower connectivity (and efficiency; Fries, 2015). Therefore, coherence between pre and postsynaptic neurons is required for efficient communication. In the case of absence of coherence (as in the case of a “disconnected brain due to ageing), performance is impaired.

In this sense, alpha tACS (α-tACS) may be a suitable combination for SoP training. For instance, α-tACS induces preferential phase synchronization of fast spiking neurons, thus resulting in an entrainment process of alpha oscillations (Huang et al., 2021). Moreover, alpha band is thought to work as a brain timer, setting up excitation and/or inhibition microstates, which will optimize incoming information processing or inhibition (Mathewson et al., 2011). Furthermore, α-tACS is able to modulate temporal resolution of human vision by acting over the segregation/integration time window of visual information, thus inducing participants to integrate more often two stimuli into one percept (Battaglini et al., 2020); or even to modulate information transfer in the premotor-cerebellar loop during learning (Schubert et al., 2021).

Interestingly enough, alpha activity seems to be one of the most distinguishable alterations in the human brain due ageing, with several studies showing changes in terms of alpha power, coherence and peak frequency in older adults, when comparing to younger ones (Purdon et al., 2015; Beese et al., 2019; Elshafei et al., 2020).

Here the goal is to use each participant’s endogenous peak alpha frequency to guide endogenous alpha phase-tACS (α-tACS) to further increase brain connectivity within brain networks (Bächinger et al., 2017).

In this sense, the current proposal aims to combine two interventions that have already shown promising results: a specific SoP training that has been shown to produce results in the elderly (Edwards et al., 2017) and an intervention that has been shown to entrain brain activity (Huang et al., 2021), as a means of increasing brain connectivity (Bächinger et al., 2017).

## Methods

### Purpose, Primary, and Secondary Outcomes

#### Primary Outcomes

The primary outcome will be changes from baseline in the *Useful Field of View* (*UFOV*) Assessment at week 3. UFOV is a good indicator of visual processing speed (Ball et al., 1988). The endpoint at week 3 was chosen because it is at the end of the intensive phase, and will be complemented by a co-primary endpoint at week 6 (after booster sessions). Long-term effects will be assessed at 1, 3, and 6 months after the stimulation has ended.

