### Sample Size

No previous studies using tACS and SoP have used UFOV as a primary outcome, and as such, we are using the UFOV test-retest data from Bentley et al. (2012). For older adults the mean (SD) test-retest difference (i.e., consistency between measurements at two different timepoints on the same sample) between UFOV applications was 56.2 (74.8). In order to show an effect, our intervention should at least surpass the mean test-retest difference. So we ran three different scenarios: 0.50, 0.75, and 1.00 SD below mean difference for older adults, with a power of 0.8 and alpha of 0.05. In these scenarios, a minimum of 17 participants and a maximum of 64 per group would be required in order to detect a Cohen’s d of 1 and 0.5, respectively. However, these values were above the mean test-retest difference for younger adults, namely 31.5 (43.7). As such we used this value as our cut off point, and with a power of 0.8 and alpha of 0.05 we would need at least 98 participants per group. If an attrition rate of 10% is considered, 109 participants per group will be required. However, having trial feasibility into consideration, we decided to conduct a interim analysis for futility as soon as 19 participants per group are reached, then at 32 participants per group and finally at 71 participants per group (always considering the 10% attrition rate).

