### Assessments

#### Useful Field of View (UFOV)

UFOV is a very well validated instrument to assess speed of processing and will be administered before the intervention and at the end of week 3 (see Figures 1, 2). This time point was chosen in order to minimize loss to follow-up. As there is some evidence that there may be a ceiling effect of CT (which may be the case for SoP also), we will also collect a co-primary endpoint at the end of the training (i.e., week 6; see Figures 1, 2).

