### Statistical Analysis

#### Primary Outcome

We expect that all groups, after the intervention, have increased performance in the UFOV scores, however we also expect that the group with the combined active α-tACS and SoP training would present the largest increase in scores, when comparing to either intervention alone. This will be tested by calculating the delta (week 3 or 6—baseline), and by performing independent one-way ANOVAS with intervention as a factor. Moreover, with the present design, we can track the intervention effects in several time points, namely between baseline, at week 3 and 6 of the interventions. This will be performed by means of an exploratory mixed model-ANOVAS, with time as within subject factor and intervention as between subject factor. As we cannot control at this point for several variables such as gender, depression or years of education, if there are significant differences between groups after randomization, we will include those covariates in the analysis, performing ANCOVAS instead of ANOVAS.

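### Week 3 and week 6 UFOV are both made primary, but the sample size is that of a single test, so the stated alpha of 0.05 and power of 0.80 hold under neither reading of co-primary

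*Protocol article*

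**What the plan says.** All references are to the protocol article.

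- *Primary Outcomes* opens with one time point: "The primary outcome will be changes from baseline in the *Useful Field of View* (*UFOV*) Assessment at week 3". It then says that this "will be complemented by a co-primary endpoint at week 6 (after booster sessions".
- *Assessments, Useful Field of View (UFOV)* gives limiting loss to follow-up as the reason for week 3. It raises a possible ceiling effect of training and says "we will also collect a co-primary endpoint at the end of the training".
- *Statistical Analysis, Primary Outcome* gives the test: "This will be tested by calculating the delta (week 3 or 6—baseline), and by performing independent one-way ANOVAS with intervention as a factor". It states no alpha for these tests, no order, and no rule for combining them.
- *Sample Size* has one calculation: "with a power of 0.8 and alpha of 0.05 we would need at least 98 participants per group". Attrition of 10% raises this to 109 per group, and the Abstract gives 327 in total.
- *Trial Design, Setting, and Registration* describes the three-arm trial as exploratory.

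**The concern.** Two primary time points need a rule. If success at either week is enough, there are two chances of a false positive. If both weeks are required, which is the usual meaning of co-primary, there is no inflation, but the chance of succeeding twice is lower than the chance of succeeding once. A sample size worked out for one test matches neither case.

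The practical risk is a split result. The article itself allows that the effect may level off during training, so one week could be significant and the other not. As written, the article does not say whether that is a positive trial.

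**Working it through.** **1. Reproduce the sample size.** Inputs from *Sample Size*: test-retest difference 56.2 (SD 74.8) in older adults and 31.5 (SD 43.7) in younger adults, alpha 0.05, power 0.80. The article does not state the effect size or whether the test is two-sided; both are inferred here.

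- Difference: 56.2 − 31.5 = 24.7
- Root-mean-square SD: √((74.8² + 43.7²)/2) = 61.26
- d = 24.7/61.26 = 0.403
- Two-sample t-test, two-sided 0.05, power 0.80: n = 97.5, so **98 per group**; power at 98 is 0.802
- Attrition: 98/0.9 = 108.9, so **109**; 3 × 109 = **327**

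The other variants tried do not give 98: SD 74.8 alone gives 145, SD 43.7 alone gives 51, and a one-sided test gives 77. The article's 17 (d = 1) and 64 (d = 0.5) also reproduce with the two-sided t-test. The trial is therefore sized for one two-group comparison, at one time point, at undivided alpha.

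**2. Two time points.** Assumptions: 98 per group analysed at both weeks, and correlation ρ between week 3 and week 6 change from 0 to 0.9 (not given in the article). For power, the effect is d = 0.403 at both weeks; in the three-arm ANOVA one arm differs by 0.403 from two equal arms. There were 20,000 simulated trials per setting.

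| ρ | Error, either week suffices (three-arm ANOVA) | Power, both weeks required (three-arm ANOVA) | Power, both weeks required (two-group test) |
|---|---|---|---|
| 0 | 0.099 | 0.696 | 0.644 |
| 0.3 | 0.095 | 0.720 | 0.670 |
| 0.5 | 0.090 | 0.736 | 0.695 |
| 0.7 | 0.084 | 0.760 | 0.715 |
| 0.8 | 0.079 | 0.767 | 0.736 |
| 0.9 | 0.073 | 0.787 | 0.748 |

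Checks at ρ = 0: exact error is 1 − 0.95² = 0.0975, and two-group joint power is 0.802² = 0.643. Both agree with the simulation. At a single week the three-arm ANOVA has power of about 0.83 to 0.84 in this scenario.

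**3. Splitting alpha instead.** At 0.025 per week, power of 0.80 at each week with the two-group test needs 118.2, so 119 per group. With attrition this is 119/0.9 = 132.2, so 133, and 3 × 133 = 399. Staying at 98 gives about 0.71 at each week.

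**The case against.** Several points can fairly be made for the article.

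- *The rule may be in the analysis plan or full protocol.* An article need not print a testing order, and the missing order alone would not be a finding. But the definition of two primary time points and the one-test sample size are both set here, and they do not fit each other. A later document could restore the fit without changing N by ranking the two weeks, and then week 6 would no longer be co-primary.
- *Full alpha is not written beside the ANOVAs.* This is correct. It is inferred because 0.05 is the only alpha given and 98 reproduces without a split.
- *The trial is exploratory.* This lowers the stakes. Yet the article fixes alpha, power and N, and its statistical section applies the exploratory label to the mixed-model analysis rather than to the change-score ANOVAs.
- *There is a hint of ranking.* Week 3 is named first and week 6 complements it. This makes a free choice after the data less plausible, but the co-primary label, used twice, leaves the rule open.
- *The planned ANOVA loses less power than the two-group test.* This stands, and both sets of figures are given.

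A reader might infer a larger problem by counting comparisons of the combined arm with each single intervention at each week. The article expects the combination to do best but names no such contrasts in its analysis. Errors or power losses computed that way would also come partly from having two comparators rather than two weeks. A reader might also want the rule tied to the UFOV score behind the sizing figures. The article lists four subtests and does not say which score those figures describe, so that cannot be settled from it.

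**Conclusion.** The concern holds as a mismatch between two primary time points and a one-test sample size. Under the either-week reading the error is moderately above 5%. Under the both-weeks reading the shortfall from 0.80 is about 1 to 10 percentage points for the planned ANOVA and 5 to 16 for the two-group test; it is smallest when the two changes are highly correlated.

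That the mismatch exists is clear from the text. Its size rests on the back-calculated d, equal effects at both weeks and the assumed correlation. If the week 6 effect differs from the week 3 effect, the both-weeks power changes accordingly. It would be too strong to say that the trial's error rate is inflated: this is so only if either week counts as success, and the article does not say that. The point deserves correction, but it does not undermine the design.

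**What to change.** Make UFOV change at week 3 the single primary time point, which is how *Primary Outcomes* begins and what the UFOV assessment section justifies by loss to follow-up. Relabel week 6 as key secondary and test it at 0.05 only if week 3 is significant at 0.05. This fixed order holds the error across the two time points at 5% and leaves the 98/109/327 calculation as it stands.

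The change is one of wording in the protocol, the analysis plan and the registry entry, best made before any unblinded look at the data. The cost is that no formal week 6 claim is possible if week 3 fails. If the sponsor wants both weeks to carry equal standing, the success rule should be stated and the sample size recalculated for it; with alpha split equally and power of 0.80 at each week, that means 399 participants instead of 327.

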#### Secondary Outcomes

##### NIH Executive Abilities: Measures and Instruments for Neurobehavioral Evaluation and Research (NIH EXAMINER)

Aims at providing a robust measure of executive functioning, namely in terms of working memory, inhibition, set shifting, fluency, insight, planning, social cognition, and behavior (Kramer et al., 2014). Moreover, it seems to be sensitive enough to detect cognitive changes even in pre-symptomatic frontotemporal lobar degeneration (Staffaroni et al., 2020). It will be used to assess for potential transfer effects from speed of processing towards several core skills underlying executive function.

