#### Endogenous Alpha-Transcranial Alternating Current Stimulation (α-tACS)

Participants will do a run-in phase (EEG without α-tACS) during the first 5-min of each training session in order to trace the individual alpha frequency (IAF) over occipital regions (defined as the maximum alpha value within the 7–13 Hz range), which will then be used to deliver the 2 mA α-tACS (based on the IAF) over the prefrontal cortex (PFC; i.e., F3 and F4) for 20-min, using 35 cm^2^ sponges. The PFC was chosen due to his age-related decline (Fjell et al., 2013) and to his involvement in visual target processing (Madden et al., 2004). For the sham tACS, a 45-s of active α-tACS will be applied. This will allow to mimic the initial sensation of tACS. The computer screen will randomly flicker across the experiment for the sham tACS, because active tACS bellow 40 Hz is likely accompanied by visual flicker sensations. Thus, we plan to use the computer screen to mimic this flickering for the sham tACS condition. In order to continuously monitor electroencephalographic (EEG) activity and deliver α-tACS during task performance, a custom Loop-IT solution from Neurocare (Germany) will be used.

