### Outcomes

Main outcome will be the Useful Field of View (UFOV) test for speed of processing and attention (Ball et al., 1988). The UFOV is a test that was designed to evaluate daily life difficulties experienced by the elderly, such tasks that require divided visual attention and have to be undertaken rapidly (speed of processing). The four-subtest stimulus will be used for the computerized version, namely identification alone; divided attention; selective attention; selective attention in conjunction with same/different discriminations will be used (Edwards et al., 2006). UFOV is expected to be completed in 10 min and participants are asked to touch the screen as soon as they identify a target (i.e., a car silhouette inside a box), with the target exposure ranging from 16.67 to 500 ms. In order to probe divided attention, a peripheral target is added to the central target. For the selective attention, distractors are added; while for the more demanding version, there are two central targets, and participant are asked to make a judgment if they are similar or not.

The NIH EXAMINER battery will be used for assessing transfer effects of the intervention to untrained domains. The NIH EXAMINER comprises cognitive control, verbal fluency, and working memory assessments (Possin et al., 2013). Namely, NIH EXAMINER is a computerized version of several tasks targeting working memory, inhibition, set shifting, fluency, insight, planning, social cognition, and behavior, which allows for the calculation of a composite score (Kramer et al., 2014). As the time to complete several tasks is performance dependent, we expect participants to complete the NIH EXAMINER between 30 and 60 min.

Resting state EEG will be used as a surrogate outcome, and will be performed before and immediately after the intervention in order to assess power spectral density changes, cross frequency couplings and coherence among electrodes. Participants will also perform a short auditory oddball task (Fz, Cz, Pz, and Oz) because the P3 wave is a good marker of brain’s speed of processing. Analysis will be considered exploratory if the dropout rate reaches 20%.

At week 3 and 6 outcomes will be collected the following business day, due to particular characteristics of the sample.

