#### Secondary Outcomes

##### NIH Examiner

The NIH EXAMINER battery is important to address transfer effects to untrained domains, such as executive function, insight or social cognition and behavior. Chi-square tests will be used for week 3 and 6 reliable change indexes. Reliable Change Index (RCI) will be calculated by using the standard deviation of the reference data-set, and the test-retest reliability (Cronbach’s alpha). As we want the RCI, the difference between measurements will be compared to the S_Diff_ multiplied by 1.96 (Jacobson and Truax, 1991). This will allow for a categorial YES/NO variable for the chi-square tests. Moreover, with the present design, we can track the intervention effects in several time points, namely at baseline, week 3 and 6 of the treatment. This will be performed by means of chi-squares, with time as within subject factor and intervention as between subject factor.

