This proposal has some ethical concerns that need to be addressed according to national and international regulations. The participation of subjects will always be informed, consented and voluntary. If participants are vulnerable individuals or groups then research activities will only be performed if all potential risks are minimized, and the outcome of research is valuable enough that can have an impact in their quality of life, mental health or well-being. The current proposal involves the use of physical techniques, which are not invasive and do not represent more than minimal risk.

Therefore, the current proposal aims at combining speed of processing training (SoP) with endogenous alpha tACS, by developing an EEG-tACS closed loop solution. Additionally, we plan to use executive measures to assess if speed of processing training transfers to other higher order cognitive domains. Furthermore, we want to explore how changes in cognition are related to changes in the brain, as assessed by the EEG, namely connectivity across proximal and distal regions, and coupling with other frequencies of interest, such as the alpha-gamma amplitude coupling. In sum, the results of this project will further provide important insights into the mechanisms underlying EEG-tACS closed-loop coupled with cognitive training to enhance Speed of Processing in people with MCI. This proposal will allow us to test a new intervention, at the same time that we explore the mechanism by which the intervention works, and to probe for potential biomarkers that may be useful to guide future interventions.

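### The NIH EXAMINER is to show transfer from speed training, but its only stated between-arm test cannot tell a training effect from a direct effect of prefrontal stimulation

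*Protocol article*

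**What the plan says.** **Meaning given to the outcome.** Secondary Outcomes says of the NIH EXAMINER: "It will be used to assess for potential transfer effects from speed of processing towards several core skills underlying executive function". The Abstract wants to "assess if those changes in speed of processing transfer to other cognitive domains". The Discussion closes with: "we plan to use executive measures to assess if speed of processing training transfers to other higher order cognitive domains". The Outcomes section is looser: "The NIH EXAMINER battery will be used for assessing transfer effects of the intervention to untrained domains". The NIH Examiner paragraph of the Statistical Analysis likewise speaks only of transfer to untrained domains.

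**Arms.** The Abstract and Discussion describe SoP training plus active α-tACS, SoP training alone, and active α-tACS alone. The intervention sections describe a sham version of each component. Active current is delivered "over the prefrontal cortex (PFC; i.e., F3 and F4) for 20-min". Two of the three arms therefore receive it in full. The Discussion acknowledges that there is no arm with both components sham.

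**Analysis.** "Chi-square tests will be used for week 3 and 6 reliable change indexes". Each participant is classed as reliably changed or not, and intervention is the between-subject factor. No pairwise contrast is named for this outcome. Under Long-Term Effects, EEG measures are to be correlated with the reliable change indexes. Nothing relates change on the EXAMINER to change on the UFOV.

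**The concern.** The stated interpretation is specific: executive function changes because speed of processing, or the training of it, carries over. The stated test is not specific. A chi-square across three arms asks only whether the proportions with reliable change differ somewhere.

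The outcome is executive function and the current is placed over the prefrontal cortex, so a direct effect of stimulation is a plausible rival explanation. If stimulation alone raised EXAMINER scores, both arms with active current would rise together, SoP alone would lag, and the chi-square would be significant with no transfer of training at all. The Discussion stresses how mixed the evidence on transfer of cognitive training is, so a mislabelled result here would matter.

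**Working it through.** **Step 1. The number per arm.** The Sample Size section gives 98 per group, based on the UFOV. It can be reproduced from that section's test-retest figures, 56.2 (SD 74.8) and 31.5 (SD 43.7):

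- difference = 56.2 − 31.5 = 24.7
- pooled SD = √((74.8² + 43.7²)/2) = 61.26
- d = 24.7/61.26 = 0.403
- two-sided t-test, alpha 0.05, power 0.80: 97.5, rounded up to 98
- with 10% attrition: 98/0.90 = 108.9, rounded up to 109; 3 × 109 = 327

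The pooling and the two-sided alpha are inferred, because they reproduce the plan's figures. The 98 serves below only as the evaluable number per arm.

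**Step 2. Why the three-arm test cannot separate the explanations.** Let b be the reliable-change rate without the effective component and s the rate with it. In the order (combination, SoP alone, tACS alone):

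- pure stimulation effect: (s, b, s)
- pure training effect: (s, s, b)

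With equal arms of size n and observed counts x₁, x₂, x₃, the Pearson statistic is Σ(xᵢ − n·p̄)² / (n·p̄(1 − p̄)), where p̄ = Σxᵢ/(3n). Swapping two arms does not alter it. Its distribution is therefore the same under both patterns, and so is its rejection rate, whatever b and s are.

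**Step 3. Size.** The document gives no reliable-change rates, so b and s are assumptions, shown over a range. Each scenario used 20,000 simulated trials, 98 per arm, and a Pearson chi-square at 0.05.

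| Assumed b, s | Three-arm test, pure stimulation | Three-arm test, pure training | Combination vs SoP alone, pure stimulation | Combination vs tACS alone, pure stimulation | Combination vs tACS alone, pure training |
|---|---|---|---|---|---|
| 5%, 15% | 67% | 66% | 67% | 5% | 67% |
| 10%, 20% | 49% | 49% | 51% | 5% | 50% |
| 10%, 25% | 82% | 83% | 80% | 5% | 81% |
| 10%, 30% | 97% | 97% | 95% | 5% | 95% |
| 20%, 35% | 67% | 68% | 66% | 5% | 66% |

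The differences between the second and third columns are simulation noise, by Step 2. In the last two columns, the contrast that holds stimulation constant stays at its nominal level when only stimulation works, and responds when training works.

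**Step 4. The safeguard in the design.** Under a pure stimulation effect, the combination is significantly better than both other arms in only 2% to 3% of trials. The data can expose the problem if the transfer claim rests on the right comparison.

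**The case against.** The strongest defence is that the design already contains the control. There is an active-tACS-alone arm and a sham training task. The Discussion names the EXAMINER as the measure of untrained domains and asks whether the combination is better than either intervention alone. That implies combination versus tACS alone, and a pure stimulation effect would rarely pass it. This stands. A reader might infer that such an effect **would** be reported as transfer, but the documents support only that it **could** be. Nowhere do they say that any difference between arms will be called transfer, and the Outcomes and NIH Examiner paragraphs do not attribute gains to speed.

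A reader might also infer that combination versus SoP alone says nothing about transfer. That goes too far. The Introduction adds alpha stimulation because alpha activity is linked to speed of processing. Stimulation might enlarge the speed gain, and that gain might then spread to executive tasks. The contrast mixes that route with a direct prefrontal effect.

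The support for a direct effect is limited. The Introduction says "We have previously shown that we were able to modulate cognition using transcranial direct current stimulation (tDCS), namely on executive functioning", which concerns direct-current stimulation. It makes an effect of α-tACS plausible and does not show one.

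Finally, pairwise contrasts on a secondary outcome are often left to a statistical analysis plan, and this trial calls itself exploratory. A missing list of contrasts would be no finding. The point rests instead on what the article states: a specific causal reading in Secondary Outcomes and the Discussion, beside a test that cannot support it.

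**Conclusion.** The point holds as a mismatch between a stated interpretation and a stated test. It is not a confounding that the design cannot resolve. The three-arm chi-square is as likely to be significant under a pure stimulation effect as under a pure training effect of the same size. That equality needs only equal arm sizes.

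The rates themselves (about 82% at 10% versus 25%, about 67% at 5% versus 15%, about 50% at 10% versus 20%) rest on assumed reliable-change proportions and 98 evaluable per arm. They show that the risk is material if stimulation acts directly; they do not estimate how likely that is.

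Two limits remain whichever contrast is named. Combination versus tACS alone shows an effect of training given stimulation, not that the effect runs through speed of processing. Without a double-sham arm, change within the SoP-alone or tACS-alone arm cannot be separated from practice or placebo effects.

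**What to change.** 1. In the NIH Examiner paragraph of the Statistical Analysis, name combination versus active tACS alone, where stimulation is held constant, as the test of transfer from SoP training.
2. Report combination versus SoP alone as the effect of adding stimulation. State that it cannot separate a direct prefrontal effect from transfer of stimulation-enhanced speed gains.
3. Align the NIH EXAMINER text under Secondary Outcomes and the closing paragraph of the Discussion with these two readings.
4. Optionally, add a regression of EXAMINER change on UFOV change with arm in the model. Label it supportive only: it is a non-randomised association, which shared practice gains or a shared response to stimulation could produce without transfer.

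The cost is a few sentences and, if wanted, one extra model on data already collected. The downside is a narrower transfer claim than a significant three-arm test would seem to allow.
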